### Study Eligibility

Participants will include approximately 500 adults who smoke cigarettes and access the OTH (ie, phone or web) seeking smoking cessation treatment. Participants are eligible for the study if they meet the following criteria: (1) demonstrate interest in participating in this study by giving approval to the OTH provider to share contact details with the study research team, (2) provide proof of a valid Oklahoma residential address (eg, sending a text message of their photo ID or a photo ID along with a piece of stamped mail that was sent to them), (3) score 4 or higher on the Rapid Estimate of Adult Literacy in Medicine—Short Form (REALM-SF) [25] indicating greater than sixth-grade English literacy level, (4) are willing to quit smoking within 21 days after the randomization phone call, (5) currently smoke 5 or more cigarettes per day, (6) agree to complete daily 10- to 30-second app-prompted check-ins and 27 weekly 3- to 5-minute surveys on their personal smartphone, (7) own an active Android smartphone that is compatible with the Insight platform [26], (8) agree to install the Insight application onto their personal phone, (9) are 18 years of age and older (participant age has ranged from 18 to 80 years in similar trials with most participants reporting that they are 40-50 years of age), and (10) agree to complete the 27-week postrandomization follow-up assessment (which includes biochemical verification for those who report smoking abstinence).

### Procedure

Individuals who contact the OTH for smoking cessation services via the phone or web are asked whether they are interested in participating in a smoking cessation research study. Contact information for interested individuals is shared with OKquit research team members who then send a web-based Research Electronic Data Capture (REDCap) study screener link to these individuals. Those who complete the 5-minute REDCap screener and meet the initial study inclusion criteria then complete an enrollment call, which includes the informed consent process and a full study eligibility assessment. Those who enroll in the study receive instructions about how to download the Insight app onto their personal smartphone, and they are given 7 days to complete the 30-minute app-based baseline survey. Following completion of the baseline survey, research staff contact participants to randomize them into an intervention group. Randomization is stratified based on self-reported race and ethnicity (non-Hispanic White vs minoritized race and ethnicity), biological sex at birth (male vs female), and number of cigarettes smoked per day (20 vs ≥20). During the randomization call, all participants are asked to use the app to select a quit date within the next 21 days, are given instructions on how to access intervention content, and are instructed on how to complete the prompted daily check-ins and weekly surveys. Following randomization, participants interact with their assigned intervention for the 27-week study duration. Those who report abstinence from smoking during the 26th weekly survey are mailed a Bedfont carbon monoxide monitor that pairs with the Insight app by pressing the power button on the device, and they are asked to submit a breath sample for abstinence verification. Participants are also prompted to complete a 27-week follow-up assessment via the Insight app. The study flow is shown in Figure 1.

During the randomization call, research staff review the “App Instructions” button, which explains all app features (see Figure 2), walk participants through the schedule of daily check-ins and weekly surveys, and explain that participants will receive a US $5 for completing each weekly survey. The US $5 weekly survey is available on Saturdays via a button in the app and via app prompts. When participants do not complete the weekly survey, research staff contact them via text, call, or email to check in and remind them of the importance of completing the daily check-ins and weekly surveys. The day after randomization, the app begins to prompt a brief daily check-in 30 minutes after waking, and participants select up to 5 additional brief check-ins they would like to receive for that day. All participants are prompted to complete the daily check-ins for the entire 27-week study duration.

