### Measures

#### Overview

The initial prescreener survey is completed via REDCap. The screener collects individual contact information and demographic information (eg, age, race, and biological sex at birth), average cigarettes smoked per day, and level of desire to quit smoking. The baseline assessment (30 minutes), weekly surveys (3-5 minutes each), daily check-ins (10-30 seconds), and 27-week follow-up assessment (20 minutes) are collected via the Insight app. See Table 2 for study assessments and administration schedule. For daily check-ins and weekly surveys, the phone rings and vibrates to prompt the participant to complete the assessment. If the participant does not respond after 5 prompts, the check-in/survey is automatically rescheduled up to 3 times 15 minutes later. Assessments collect information about several factors related to smoking, smoking lapse, and health. Participants are instructed to self-initiate “About to Slip” and “Already Slipped” assessments and to initiate the “Set New Quit Date” assessments when they want to set a new quit date. Each check-in and survey are date-, time-, and geolocation-stamped for future examination.

**Table 2 table2:** List and timeline of study measures.

Measure	Screener	Baseline	Follow-up
Screening Questionnaire	✓		
Phone Call Screener	✓		
Rapid Estimate of Adult Literacy in Medicine—SF (REALM) [25]	✓		
Tobacco History Questionnaire		✓	✓
Heaviness of Smoking Index [28]		✓	✓
Self-Efficacy Scale/Confidence [29]		✓	✓
Demographic/Background Information Questionnaire		✓	
MacArthur Scale of Subjective Social Status [30]		✓	✓
Overall Anxiety Severity and Impairment Scale (OASIS) [31]		✓	✓
Overall Depression Severity and Impairment Scale (ODSIS) [32]		✓	✓
The Patient Health Questionnaire-4 (PHQ-4) [33]		✓	✓
Financial Strain Questionnaire [34]		✓	
Perceived Stress Scale [35]		✓	✓
The Everyday Discrimination Scale (Brief version) [36]		✓	
The Pandemic Stress Index		✓	
Perceived Social Support Questionnaire [37]		✓	
Religious Participation [38,39]		✓	✓
Self-Rated health [40]		✓	✓
Health Related Quality of Life [41]		✓	✓
Alcohol Use Disorders Identification Test (AUDIT-C) [42]		✓	✓
Marijuana/Cannabis Use Behavior		✓	✓
BRFSS Inadequate Sleep [43]		✓	✓
Short Scale of Anxiety Sensitivity Index (SSASI) [44]		✓	✓
Cannabis Use Disorder Identification Test Short Form [45]		✓	✓
Weekly EMA^a^ items		✓	✓
Smoking Status items			✓
System Usability Scale [46]			✓
Treatment Quality and Satisfaction Survey			✓

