### Statistical Analysis

Descriptive statistics for continuous variables will include mean, SD, and quantiles, and categorical variables will be summarized as percentages and counts. We hypothesize that participants randomly assigned to the OKquit group will have significantly higher rates of biochemically verified 7-day point prevalence smoking abstinence than those assigned to SC at 27 weeks post randomization. We will use a chi-square test or Fisher exact test to compare the proportion of participants in the treatment conditions (ie, OKquit and SC) who are biochemically verified as abstinent (ie, iCO <7 ppm, and self-reports show no smoking in the past 7 days) 27 weeks after randomization. We will conduct the analysis using the intention-to-treat assumption wherein participants who are lost to follow-up or fail to complete the iCO evaluation will be classified as not abstinent. Prior to analyzing the data, we will examine the missing rate and patterns of missing data. If the missing rate is high, then we will explore sequential multiple imputation with at least 20 imputed data files as described by Raghunathan et al [47]. The analysis results from sequential multiple imputation data will be compared with those from the available data and intention-to-treat analyses. Based upon previous studies [48], we expect that 9% of those receiving the SC intervention will be biochemically confirmed abstinent at the 27-week post–quit follow-up, and based upon our pilot work, we expect that 18% of those receiving the OKquit treatment will be abstinent at the 27-week postquit follow-up visit [19,20]. With alpha values of .05 and 250 participants in each group, we have 84% power to detect a 9% difference in biochemically confirmed 7-day point prevalence abstinence at 27 weeks (ie, 45/250, 18% abstinent in the OKquit group vs 22/250, 9% abstinent in the SC group) by using Pearson chi-square test. In addition to the chi-square test or Fisher exact analysis, we will perform logistic regression analyses to determine whether the odds of abstinence vary by other baseline characteristics (eg, sex, race, and ethnicity). Finally, we will examine interactions between treatment condition and sex and race (separately) to identify potential differential effects on abstinence.

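### Randomization is stratified by three factors, but the primary test uses none of them; one of the factors is also misprinted

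*Protocol article*

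**What the plan says.** The Procedure section names three randomization factors. The first is given as "self-reported race and ethnicity (non-Hispanic White vs minoritized race and ethnicity"). The second factor is sex, split into two levels. The third is the smoking rate, which the article prints as "number of cigarettes smoked per day (20 vs ≥20"). The first two are proper two-level splits. Under Study Eligibility, participants must "currently smoke 5 or more cigarettes per day", and no upper limit is given. The cut for cigarettes per day is not restated anywhere else in the article. The Overview of Measures shows that the screener already collects "average cigarettes smoked per day, and level of desire to quit smoking".

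For the primary outcome, the Statistical Analysis section says: "We will use a chi-square test or Fisher exact test to compare the proportion of participants in the treatment conditions". It adds logistic regressions to see whether the odds of abstinence differ by other baseline characteristics, with sex, race and ethnicity as examples. It does not describe a treatment comparison adjusted for the randomization factors, and it does not name cigarettes per day as a covariate.

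**The concern.** Stratified randomization balances the arms within strata, so stratum differences add almost nothing to the real sampling error of the difference between arms. An unstratified test still counts those differences as noise. If smoking rate, sex or race and ethnicity predict quitting, its standard error is a little too large. The test then rejects a true null less often than 5% and gives up some power. The trial has gone to the trouble of stratifying and does not use the benefit in its main comparison.

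The misprint matters for the same reason. An analysis by strata has to use the levels that were randomized, and the smoking-rate levels as printed cannot be used literally.

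**Working it through.** **1. The plan's own power figure.** Inputs from the Statistical Analysis section: 18% vs 9%, 250 per arm, alpha .05. Sidedness is not stated; two-sided is assumed.

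- Pooled rate: (0.18 + 0.09)/2 = 0.135.
- Null standard error: √(2 × 0.135 × 0.865/250) = 0.03057.
- Alternative standard error: √((0.18 × 0.82 + 0.09 × 0.91)/250) = 0.03030.
- Power: Φ((0.09 − 1.96 × 0.03057)/0.03030) = Φ(0.993) = 84.0%.

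This agrees with "With alpha values of .05 and 250 participants in each group, we have 84% power to detect a 9% difference". Using the printed count of 22/250 = 8.8% gives 85.8%. Neither figure depends on the points below.

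**2. Why the unstratified test is conservative.** The unstratified test uses the variance p̄(1 − p̄). Under stratified allocation the relevant variance is the average of p_s(1 − p_s) over strata, which equals p̄(1 − p̄) − Var(p_s). The ratio of true to assumed variance is therefore r = 1 − Var(p_s)/[p̄(1 − p̄)]. The actual two-sided error is 2[1 − Φ(1.96/√r)].

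The article gives no stratum effects, so two sets of odds ratios are assumed, one per factor. For this formula, 2 × 2 × 2 = 8 equal strata with an average rate of 9% are also assumed, so p̄(1 − p̄) = 0.0819.

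| Assumed odds ratios | Stratum rates run from | Var(p_s) | r | Actual error |
|---|---|---|---|---|
| 0.7, 0.8, 0.5 (moderate) | 4.7% to 14.9% | 0.00106 | 0.987 | 4.9% |
| 0.5, 0.7, 0.35 (stronger) | 2.8% to 19.3% | 0.00268 | 0.967 | 4.6% |

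**3. Simulation.** Settings: 500 participants, 8 strata, blocked allocation within strata, 6,000 replicates, 9% control rate. The treatment odds ratio is (0.18/0.82)/(0.09/0.91) = 2.22.

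| Assumed effects | Pearson power | Cochran-Mantel-Haenszel power | Gain |
|---|---|---|---|
| Moderate | 84.2% | 84.7% | 0.5 points |
| Stronger | 81.4% | 82.5% | 1.1 points |

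The unstratified null rejection rate under the stronger effects was about 4.3%. Its Monte Carlo standard error is √(0.043 × 0.957/6,000) = 0.26 points, so it is compatible with the 4.6% in step 2. A repeat under the same assumed odds ratios gave gains of about 0.4 to 1.2 points and null rejection of about 4.4% to 4.7%.

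The lower power in the stronger row is not a shortfall in the plan. Holding the within-stratum odds ratio at 2.22 brings the average OKquit rate slightly below 18%. Only the difference between the two tests is of interest.

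**4. The printed smoking-rate levels.** Each whole number from 5 to 60 per day was placed in the levels 20 and ≥20:

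- 5 to 19: neither level.
- 20: both levels.
- 21 and above: the second level only.

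Reading the first level as <20 puts every value in exactly one level. So would ≤20 vs >20, but that reading requires both printed levels to be wrong.

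**The case against.** The strongest objection is that an unadjusted chi-square after stratified randomization is a legitimate primary analysis that errs on the safe side, and that the gain is about one point of power under effects the article does not supply. All of this stands. It makes the change an improvement, not the repair of an invalid test. It may also be said that covariate adjustment is commonly left to a statistical analysis plan that is not shown. Here, though, the article names its primary test, so the proposal replaces a stated method and does not fill a gap. The additional logistic regressions mention sex and race, but as predictors of abstinence and not as a stratification-adjusted treatment comparison.

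On the misprint, a reader might infer that smokers of 5 to 19 per day could not be allocated, or that the level for 20-a-day smokers is unknowable. The documents support neither. The article summarises the allocation rule, and the randomization setup itself is not shown. Enrolment had reached 345 by July 2024, with no sign of difficulty in placing participants. The well-formed level ≥20 includes 20 and implies that the other level is <20. The less-than sign does survive in "iCO <7 ppm, and self-reports show no smoking in the past 7 days", so such signs were not lost throughout, but the loss of a single character in print or in text conversion cannot be excluded.

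**Conclusion.** The primary comparison does not use the factors on which the trial randomizes. It remains valid and is slightly conservative if those factors predict abstinence. The cost is small: roughly 0.5 to 1 point of power, and a type I error of about 4.3% to 4.9% instead of 5%. These sizes rest on assumed odds ratios (and, for the formula, equal strata). With weakly prognostic factors they shrink towards zero. The stated 84% power stands. A reader might take the result as showing an underpowered or biased primary test, and it does not show that.

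The smoking-rate levels are wrong as printed, but this is a wording error with a recoverable meaning. It changes no figure in the article and is no evidence of faulty allocation.

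**What to change.** 1. Make the primary comparison a Cochran-Mantel-Haenszel test stratified by the three randomization factors, or a logistic regression with treatment and those factors. Keep the unadjusted chi-square as a sensitivity analysis, and fix the choice before outcome data by arm are seen.
2. Print the smoking-rate cut as programmed (the second level implies <20 vs ≥20), confirm it against the allocation log, and use those recorded strata in the analysis.

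The cost is one changed sentence in the analysis section, one corrected sign and one check of the log. The factors are collected before randomization, so no new data or participants are needed.

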#### Biochemical Verification of Smoking Status

Participants who report smoking abstinence 26 weeks after enrollment are mailed a Bedfont iCO Smokerlyzer to complete a breath test and verify their smoking status. Step-by-step instructions are presented on the smartphone screen on how to complete an iCO test. All test results are date- and time-stamped and saved for future analysis.

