### Compensation

Participants receive compensation for completing the baseline assessment (US $20), weekly surveys (US $5 each), and the 27-week follow-up assessment (US $50) via a reloadable GreenPhire Mastercard. Participants are not compensated for completing or accessing treatment components including daily check-ins, on-demand assessments, or intervention content. Participants who report 7-day smoking abstinence at 26 weeks post enrollment (via weekly survey) and provide a breath sample are paid an additional US $20 regardless of their actual smoking status. Thus, participants may receive up to US $225 for completing all study measures. Participants can click the “Payment” button on the app home screen to review their compensation summary.

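### Breath monitors are mailed only on a week-26 report of abstinence, so some participants abstinent at week 27 have no described route to verification and count as failures on the primary endpoint.

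*Protocol article*

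**What the plan says.** Three places in the protocol article describe how a participant comes to give a breath sample, and all three look to week 26.

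- Procedure: "Those who report abstinence from smoking during the 26th weekly survey are mailed a Bedfont carbon monoxide monitor".
- Biochemical Verification of Smoking Status: "Participants who report smoking abstinence 26 weeks after enrollment are mailed a Bedfont iCO Smokerlyzer to complete a breath test".
- Compensation, on who receives the extra payment: "Participants who report 7-day smoking abstinence at 26 weeks post enrollment (via weekly survey) and provide a breath sample".

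The endpoint itself is set at week 27. Statistical Analysis defines verified abstinence as "iCO <7 ppm, and self-reports show no smoking in the past 7 days", assessed 27 weeks after randomization, and adds that "participants who are lost to follow-up or fail to complete the iCO evaluation will be classified as not abstinent".

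Study Eligibility describes a different arrangement. Participants must "agree to complete the 27-week postrandomization follow-up assessment (which includes biochemical verification for those who report smoking abstinence"), which attaches verification to the week-27 report.

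**The concern.** A participant can count as a success only with an iCO reading, and the only described way to obtain a monitor is to report abstinence at week 26. Two kinds of participant can be 7-day abstinent at week 27 and still be scored as failures:

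- (a) those who did not complete survey 26;
- (b) those who truthfully reported smoking on survey 26 and then did not smoke for the next seven days.

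Neither kind failed the test, because the plan as written never offers it to them. In practice, success requires completing one particular survey, two abstinent reports a week apart, and a breath result. That is a narrower outcome than 7-day point prevalence at week 27.

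If the loss is equal in the two arms, both observed rates and the difference between them shrink, and power falls. If it is unequal, the estimated effect is biased, in a direction the article does not determine.

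**Working it through.** **Tracing the two groups through the text.**

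1. Group (a): no survey 26, so no week-26 report, so no monitor under Procedure, Biochemical Verification or Compensation. There is then no iCO result, and Statistical Analysis scores the participant as not abstinent. Procedure has staff contact people who miss a weekly survey, but describes no other way to a monitor.
2. Group (b): smoking reported on survey 26, so no monitor, with the same result. The two 7-day windows end a week apart and need not overlap, so a truthful report of smoking at week 26 is compatible with 7-day abstinence at week 27. Participants can set a new quit date at any time, so such people can exist.
3. Study Eligibility would have both groups verified at the 27-week assessment. No section says how they would get a device. The sections therefore disagree on who is tested for the primary endpoint.

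**Reproducing the stated power.** Inputs from Statistical Analysis: 18% vs 9%, 250 per arm, alpha .05 (taken as two-sided), Pearson chi-square.

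- Pooled rate = (0.18 + 0.09)/2 = 0.135
- Null SE = √(2 × 0.135 × 0.865/250) = 0.0306
- Alternative SE = √((0.18 × 0.82 + 0.09 × 0.91)/250) = 0.0303
- Power = Φ((0.09 − 1.96 × 0.0306)/0.0303) = Φ(0.99) = 0.840

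This matches the stated 84%; exact enumeration gives 0.846.

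**Illustration, equal loss.** Let c be the share of true week-27 abstainers who reach the breath test. The article gives no value for c, so the values below are assumptions. They also assume that 18% and 9% are rates before this loss. Observed rates are 18% × c and 9% × c.

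| c | OKquit | SC | Power |
|---|---|---|---|
| 1.00 | 18.0% | 9.0% | 84% |
| 0.95 | 17.1% | 8.55% | 82% |
| 0.90 | 16.2% | 8.1% | 79% |
| 0.80 | 14.4% | 7.2% | 74% |

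**Illustration, unequal loss.**

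- OKquit c = 0.80, SC c = 0.90: 14.4% vs 8.1%, a difference of 6.3 points instead of 9.0; power 61%.
- OKquit c = 0.90, SC c = 0.80: 16.2% vs 7.2%, a difference still of 9.0 points, although with c = 0.90 in both arms it would be 16.2% − 8.1% = 8.1 points; power 88%.
- No true effect, 9% in both arms, capture 90% vs 80%: observed 8.1% vs 7.2%. Both SEs are 0.0238. The two tails are 0.057 + 0.010 = 0.067, so two-sided rejection is about 6.7% (exact enumeration 6.6%, against 4.9% with no loss).

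**The case against.** **No other route is described, but none is ruled out.** Procedure says who is mailed a monitor. It does not say that others are refused one, and a condensed article may leave the handling of a missed survey to the full protocol. This stands as a caution: a reader might infer that such people cannot be verified in practice, and the article does not show that. It does show three consistent statements of a week-26 trigger, a scoring rule that depends on the result, and an eligibility criterion that does not fit them. That is a conflict on the primary endpoint, not only an omitted detail.

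**The planning rates may already include the loss.** Statistical Analysis states the 9%, and the power calculation, in terms of biochemically confirmed abstinence. Some loss to verification may therefore be built in, and discounting again would double-count. This stands. The 84% is not wrong, and the power table is not a demonstrated shortfall.

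**A larger false-positive rate.** A reader might compute rejection with 18% in both arms, which at 90% vs 80% capture gives about 8.6%. But 18% is the rate planned for an effective app. If the app adds nothing, the planned SC rate of 9% is the natural base, which gives 6.7%. The capture values are assumptions either way.

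**Differential loss by arm.** A reader might infer it from the check-in welcome text, which tells only OKquit participants that their answers tailor their messages. That text belongs to the unpaid morning check-in. The weekly survey is paid at US $5, prompted, and followed up by staff in both arms. Differential loss is possible, but the article does not make it likely.

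**Group (b) is narrow.** The quit has to fall almost exactly between the two assessments, so the group is probably small. Payment and staff contact should also shrink group (a), but they do nothing for group (b).

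**Breath-sample timing.** Tests are date- and time-stamped, and mailing after survey 26 is reasonable lead time for a week-27 sample. The absence of a stated window is not a finding in itself.

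**Imputation.** The plan says: "If the missing rate is high, then we will explore sequential multiple imputation with at least 20 imputed data files". This is conditional and exploratory, and the article does not say whether people never sent a monitor would count as missing.

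**Conclusion.** The point holds as a should-fix. On the text shown, the mailing trigger is at week 26, the endpoint is at week 27, and an absent iCO result is a failure. Some true week-27 abstainers are therefore misclassified by the plan's own rule, and Study Eligibility contradicts the trigger. The quarrel is not with scoring missing verification as smoking, which is a stated choice. It is with never offering the test because of an answer, or no answer, a week earlier.

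The size is unknown. The figures of 82% to 74% power rest on two assumptions: equal loss of 5% to 20%, and planning rates that exclude that loss. The 6.7% rejection rate rests on assumed capture of 90% vs 80% with 9% true abstinence in both arms. None of these establishes that the trial is underpowered or biased.

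**What to change.** 1. Reconcile Study Eligibility, Procedure, Biochemical Verification of Smoking Status, Compensation and Statistical Analysis, so that one rule says who is offered a breath test and when.
2. Keep the week-26 mailing, and extend it to participants who did not complete survey 26. Also mail a monitor to anyone who reports 7-day abstinence at the 27-week follow-up and does not have one. Pair each breath sample with a 7-day smoking report.
3. For participants already past week 27, report by arm the number who self-reported abstinence but were never sent a monitor. Treat their verification as missing, not failed, in a prespecified sensitivity analysis. This count would also show the actual size of the problem.

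The cost is a limited number of extra monitors, postage and US $20 payments, plus an amendment. With 345 of about 500 enrolled by July 2024, verification would differ between earlier and later participants. Randomization should balance that difference across arms, but it should be reported.
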